#### Intervention - DIAMOND group

Patients randomized to the DIAMOND group will receive usual care after the initial CA with repeat CA at 12 and 24 months.

#### Manpower estimation

From each participating centre, 600 consecutive type 2 diabetic patients will be recruited. Each day, approximately 4-6 patients can undergo CA performed by the doctor-nurse-HCA team. We expect to complete recruitment in 6-8 months with 300 patients randomized to the usual care (DIAMOND) and 300, to structured care (JADE) (see example for suggestion of workflow).

|           | Mon                          | Tues                                      | Wed                          | Thurs                                     | Fri                          |
|-----------|-------------------------------------|--------------------------------------------------|-------------------------------------|--------------------------------------------------|-------------------------------------|
| AM | CA
of 4-6 patients               | CA
of 4-6 patients                            | CA
of 4-6 patients               | CA
of 4-6 patients                            | CA
of 4-6 patients               |
| PM | Data entry
Reminder
Education | FU clinic of 10
JADE patients by
trio-team | Data entry
Reminder
Education | FU clinic of 10
JADE patients by
trio-team | Data entry
Reminder
Education |

Assuming 4 patients daily and 20 patients weekly, 600 patients will be enrolled in 30 weeks. On average, each patient has 4 team-based visits yearly to give 1200 patient-visits. Assuming 10 patients per session, this will give 120 clinic sessions, i.e. 2 clinics weekly. The nurse-HCA will use other sessions to educate patients, manage data, recall default, check protocol adherence and risk factor control, as guided by the doctor.

#### Logistics and timeline

The following diagram summarises the flow of the study including approval of local institutional board, staff recruitment and training, use of portal and patient enrolment. We expect completion of recruitment within 6-8 months after all logistics are put in place. All patients will be followed up for at least 24 months with completion of follow up of all randomized patients, 3 years after the first patient is entered the study.

[figure not shown]

## SAMPLE SIZE CALCULATION

In this multicentre study enrolling 600 patients from sites with different health settings in Asia Pacific region, we aim to test the hypothesis whether using a doctor-nurse-HCA team will reduce all diabetes-related clinical endpoints and improve control of risk factors compared to usual care, in low, middle and high-income areas including public and private clinics as well as hospital or community-based clinics.

### Primary composite outcome

The following table summarises the hazard ratios (HR) of different diabetes-related endpoints from 3 studies (16; 20; 29), all of which have used a team approach to manage medium to high risk type 2 diabetic patients from Asia and Europe, using predefined protocols and targets. These results confirm the inter-ethnic differences in disease predisposition with Caucasians being more likely to suffer from cardiovascular disease and Chinese, from renal disease (39). Despite these differences, in all 3 studies, the HR ranged from 0.3 to 0.7 for all diabetes-related events in the team-based structured care group compared to usual care.

Summary of RCT data and 3 studies showing the effects of risk factor reduction and team-based care on clinical outcomes

| Steno study |    | baseline | 7 years | 13 years | Difference at 7 yr |
|-------------|----|----------|---------|----------|--------------------|
| LDL-C       | SC | 3.44     | 2.15    | 1.84     | 1.1 (30%)          |
|             | UC | 3.54     | 3.3     | 1.99     |                    |
| TG          | SC | 1.8      | 1.3     | 1.12     | 0.5 (30%)          |
|             | UC | 2.3      | 1.8     | 1.67     |                    |
| A1c         | SC | 8.4      | 7.9     | 7.7      | 1 (12%)            |
|             | UC | 8.8      | 9       | 8        |                    |
| SBP         | SC | 146      | 131     | 140      | 15 (10%)           |
|             | UC | 149      | 146     | 146      |                    |
| DBP         | SC | 85       | 73      | 74       | 5 (5%)             |
|             | UC | 86       | 78      | 73       |                    |
| ACEI        | SC | 20       | 97      | 91       |                    |
|             | UC | 19       | 70      | 87       |                    |
| Statin      | SC | 0        | 85      | 84       |                    |
|             | UC | 3        | 22      | 82       |                    |

| RCT data | Risk factor changes | risk reduction | Remarks         |
|----------|---------------------|----------------|-----------------|
| LDL-C    | 30%                 | 20-30%         | CVD             |
| SBP      | 14 mm Hg            | 12%            | CVD             |
| A1c      | 1%                  | 12-14%         | CVD             |
|          |                     | 21%            | all DM endpoint |
|          |                     | 21%            | all DM death    |
|          |                     | 19%            | cataract        |
|          |                     | 37%            | microvascular   |
|          |                     | 43%            | PVD             |

| Steno 13 year FU       | SC=80 | UC=80 | HR   |
|------------------------|-------|-------|------|
| death                  | 24    | 40    | 0.50 |
| CVD-death              | 9     | 18    | 0.23 |
| MI                     | 8     | 21    | 0.26 |
| stroke                 | 6     | 18    | 0.23 |
| PCI                    | 8     | 13    | 0.16 |
| revascularization      | 6     | 10    | 0.13 |
| amputation             | 6     | 14    | 0.18 |
| all CVD events         | 25    | 48    | 0.60 |
| cancer-death           | 2     | 5     | 0.06 |
| DM nephropathy         | 20    | 37    | 0.46 |
| ESRD                   | 1     | 6     | 0.08 |
| Blindness              | 2     | 7     | 0.09 |
| Progression of DMR     | 41    | 54    | 0.68 |
| Laser or macular edema | 14    | 27    | 0.34 |

| 2-year SURE Study | ≥3 target | <3 targets | HR   |
|-------------------|-----------|------------|------|
| ESRD/death/dSeCr  | 14        | 34         | 0.30 |
| dialysis          | 6         | 12         | 0.11 |
| dSeCr             | 10        | 21         | 0.18 |
| death             | 4         | 15         | 0.13 |
| MI/angina/PCI     | 4         | 7          | 0.06 |
| heart failure     | 12        | 16         | 0.14 |

| 7-year AJMC paper | SC | UC | HR   |
|-------------------|----|----|------|
| death             | 8  | 20 | 0.25 |
| death/CVS/renal   | 20 | 30 | 0.38 |

These Kaplan-Miere plots show the estimated events from these 3 studies in a 2-year period.

Chinese T2D patients with CKD (eGFR 30 ml/min/1.73m^2)  
Chan JC et al Diabetes Care 2009

[figure not shown]

Chinese T2D patients with HT (no CVD/CKD)  
So WY et al Am J Managed Care 2003

[figure not shown][figure not shown]

Caucasian T2D patients with microalbuminuria (no CVD/CKD)  
Gaede P et al NEJM 2008

[figure not shown]

Using validated risk equations and risk parameters, the JADE Program stratified patients into very high risk, high risk, medium risk and low risk groups with respective estimated annual event rate of 7%, 3%, 1.5% and 1%.

#### Original Article: Complications

**The Joint Asia Diabetes Evaluation (JADE) Program: a web-based program to translate evidence to clinical practice in Type 2 diabetes**

#### 5 year event rates

[figure not shown][figure not shown]

#### Risk levels (5-year event rate)

4: Cardio-renal complications

3: CKD or at least 3 risk factors or high risk score

2: no CKD and 2 risk factors or medium risk score

1: no CKD and 1 or no risk factor and low risk score

Chan JC et al Diabetic Med 2009

In our first year analysis of the JADE Asia Pacific Program, the majority of enrolled patients from 7 countries belonged to very high to high risk category.

#### Complications and risk factors in 3687 Asian T2D patients

[figure not shown]

So WY et al for JADE Study Group J of Diabetes 2011

We used these observations to estimate the sample size needed to give a 2-year study 80% power with an alpha value of 0.05 to confirm the superiority of team-based structured care over usual care on clinical endpoints. We used different combinations of scenarios including an annual hazard rate ranging from 0.01 to 0.10 in the usual care group and a HR ranging from 0.5 to 0.85 in the structured care group with an attrition rate of 0.2, to estimate the sample size. Using the most conservative scenario where the annual hazard rate is 0.02, i.e. 0.04 in 2 years and assuming a HR of 0.8 in the structured care group, the study will have sufficient power to confirm the primary hypothesis. For high risk patients with a hazard rate of 0.05 and those with medium risk (0.03), and assuming a modest HR of 0.8 in the structured care group, a sample size of 6626-13762 patients will give the study 80% power at an alpha value of 0.05.

|                                                     |      |       |                |      |       |       |
|-----------------------------------------------------|------|-------|----------------|------|-------|-------|
| 80% power at 0.05 alpha
minimum 2 year follow up |      |       |                |      |       |       |
| LOW RISK                                            |      |       | VERY LOW RISK  |      |       |       |
| hazard ratio                                        | 0.5  | 0.8   | 0.85           | 0.5  | 0.8   | 0.85  |
| annaul hazard rate                                  | 0.02 | 0.02  | 0.02           | 0.01 | 0.01  | 0.01  |
| hazard rate (usual)                                 | 0.04 | 0.04  | 0.04           | 0.02 | 0.02  | 0.02  |
| hazard rate (structured)                            | 0.02 | 0.032 | 0.034          | 0.01 | 0.016 | 0.017 |
| absolute difference                                 | 0.02 | 0.008 | 0.006          | 0.01 | 0.004 | 0.003 |
| sanple size in each group                           | 1239 | 8760  | 15868          | 2515 | 17838 | 32333 |
| total sample size                                   | 2478 | 17520 | 31736          | 5030 | 35676 | 64666 |
| assuming 20% attrition rate                         | 2974 | 21024 | 38083          | 6036 | 42811 | 77599 |
| number needed to treat                              | 50   | 125   | 167            | 100  | 250   | 333   |
| MODERATE RISK                                       |      |       |                |      |       |       |
| hazard ratio                                        | 0.5  | 0.8   | 0.85           |      |       |       |
| annaul hazard rate                                  | 0.03 | 0.03  | 0.03           |      |       |       |
| hazard rate (usual)                                 | 0.06 | 0.06  | 0.06           |      |       |       |
| hazard rate (structured)                            | 0.03 | 0.048 | 0.051          |      |       |       |
| absolute difference                                 | 0.03 | 0.012 | 0.009          |      |       |       |
| sanple size in each group                           | 1067 | 5734  | 13820          |      |       |       |
| total sample size                                   | 2134 | 11468 | 27640          |      |       |       |
| assuming 20% attrition rate                         | 2561 | 13762 | 33168          |      |       |       |
| number needed to treat                              | 33   | 83    | 111            |      |       |       |
| HIGH RISK                                           |      |       | VERY HIGH RISK |      |       |       |
| hazard ratio                                        | 0.5  | 0.8   | 0.85           | 0.5  | 0.8   | 0.85  |
| annaul hazard rate                                  | 0.05 | 0.05  | 0.05           | 0.1  | 0.1   | 0.1   |
| hazard rate (usual)                                 | 0.1  | 0.1   | 0.1            | 0.2  | 0.2   | 0.2   |
| hazard rate (structured)                            | 0.05 | 0.08  | 0.085          | 0.1  | 0.16  | 0.17  |
| absolute difference                                 | 0.05 | 0.02  | 0.015          | 0.1  | 0.04  | 0.03  |
| sanple size in each group                           | 474  | 3313  | 5988           | 219  | 1497  | 2695  |
| total sample size                                   | 948  | 6626  | 11976          | 438  | 2994  | 5390  |
| assuming 20% attrition rate                         | 1138 | 7951  | 14371          | 526  | 3593  | 6468  |
| number needed to treat                              | 20   | 50    | 67             | 10   | 25    | 33    |

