## **SETTING AND PATIENTS**

In this program, 600 consecutive type 2 diabetic patients will be recruited from each participating centre during a 6-8 month period, with randomization to either the JADE or DIAMOND group in a 1:1 ratio.

*Inclusion criteria*

- 1) Type 2 diabetic patients who are willing or can be persuaded to return for 'regular' follow-up at 3-4 monthly intervals
- 2) Aged  $\geq 18$  years
- 3) Patients with newly diagnosed or established disease, treated with lifestyle modification or blood glucose lowering drugs including oral agents with or without insulin
- 4) For newly diagnosed type 2 diabetic patients, their plasma glucose levels should be:
  - a) Fasting plasma glucose (PG)  $\geq 7.0$  mmol/L on 2 or more occasions, and/or
  - b) Random or 2-hour PG  $\geq 11.1$  mmol/L (after 75 gram oral glucose tolerance test) on 2 or more occasions, and/or
  - c) HbA1c  $\geq 6.5\%$

*Exclusion criteria*

- 1) Type 1 diabetes defined as a history of ketosis at diagnosis [acute symptoms with heavy ketonuria ( $>3+$ ) or ketoacidosis] or continuous requirement of insulin within one year of diagnosis (38).
- 2) Patients with reduced life expectancy (e.g. less than 6 months) due to recent diagnosis of advanced cancers (e.g. within last 2 years) and other life-threatening conditions.
- 3) Patients with a mental condition rendering them unable to understand the nature, scope, and possible consequences of the study.
- 4) Patients actively enrolled in another intervention study.
- 5) Patients who are unwilling to return for regular follow up.

**OUTCOME MEASURES***Composite primary endpoint (CRF (1-5))*

- 1) Incidence of all diabetes-related endpoints including:
  - a) cardiovascular events (acute myocardial infarction, revascularisation procedures, heart failure, unstable angina, arrhythmia, stroke, transient ischemic attacks requiring hospital admissions) and related death
  - b) chronic kidney disease (eGFR  $< 60$  ml/min/1.73m^2) or end stage renal disease (dialysis and/or eGFR  $< 15$  ml/min/1.73m^2) and related death
  - c) visual impairment (corrected visual acuity of 20/200 or worse) or eye surgery (cataract removal, retinal surgery and vitrectomy)

- d) lower extremity amputation or foot ulcers requiring hospitalizations
- e) major infections – pulmonary and non-pulmonary requiring hospitalizations
- f) all-site cancers
- g) death

Composite secondary endpoint

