## **DATA ANALYSIS**

All data will be analyzed using the SPSS statistical software (Windows 13.0 version, Chicago, USA). A p value of 0.05 or less (2-tailed) will be considered significant. For the primary composite endpoint, an intention to treat analysis will be performed including all patients randomized to both groups who have at least returned for one visit or contacted by phone once post randomization to ascertain clinical status (alive, dead or hospitalized). Descriptive analysis will be used to report all clinical and laboratory parameters. Student's t-test, Chi-squared test and Analysis of Co-variance will be used for between-group and within-group comparisons for all baseline data and endpoints, as appropriate. Kaplan-Meier curve analysis will be used to compare the incidence of primary composite endpoint between the JADE and DIAMOND group adjusted for age, sex, ethnicity and disease duration. Interaction between group assignment and covariates including age, gender, duration of diabetes (< or ≥8 years), socioeconomic group, complications, risk factors, JADE risk categories, compliance and psychological health parameters will be examined. Logistic regression will be used to determine independent predictors for achieving primary composite endpoint using all relevant covariates including age, gender, duration of diabetes (< or ≥8 years), centre characteristics, socioeconomic group, risk levels, metabolic and risk factor control, compliance, self care, psychological health parameters and intervention groups.

A per protocol analysis will be performed in the JADE group with details of intervention, where we shall compare baseline clinical profile, care processes, number of visits and use of medications between patients who develop and those who do not develop clinical endpoints. A sensitivity analysis will also be performed using hazard rates of the JADE and DIAMOND group amongst those who have defaulted.

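### The protocol claims sufficient power for the primary endpoint in a scenario it calls most conservative, but its own table needs 17520 evaluable patients there, has harder scenarios, and the visible text fixes no total enrolment

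*Protocol*

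**What the plan says.** The design target is "80% power with an alpha value of 0.05 to confirm the superiority of team-based structured care over usual care on clinical endpoints". The Data Analysis section makes the test two-sided: "A p value of 0.05 or less (2-tailed) will be considered significant".

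The scenarios considered cover an "annual hazard rate ranging from 0.01 to 0.10 in the usual care group and a HR ranging from 0.5 to 0.85", with 20% attrition. From these the text picks one: "Using the most conservative scenario where the annual hazard rate is 0.02, i.e. 0.04 in 2 years and assuming a HR of 0.8". Its conclusion for this case is that "the study will have sufficient power to confirm the primary hypothesis". No number of patients accompanies this. The next sentence gives 6626-13762 patients for hazard ratio 0.8 at annual rates of 0.05 (high risk) and 0.03 (medium risk).

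In the table below that text, the block for 0.02 per year reads "2974 | 21024 | 38083" after attrition, for hazard ratios 0.5, 0.8 and 0.85.

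Enrolment is set by site: "600 consecutive type 2 diabetic patients will be recruited from each participating centre" (Setting and Patients). The Executive Summary makes 600 a minimum per site.

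In support of the assumed effect, the Primary composite outcome subsection cites three studies and says that "the HR ranged from 0.3 to 0.7 for all diabetes-related events in the team-based structured care group compared to usual care".

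**The concern.** A statement that a study will have sufficient power needs a sample size behind it. Here the scenario is named, the table shows that it needs more than 17000 evaluable patients, and the visible text does not commit to that number or to any other total. A reader who looks for a total finds 6626-13762 in the next sentence, which belongs to higher event rates.

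The wording also suggests that a worst case has been covered, although the same table contains worse cases.

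The primary endpoint is clinical events. If the comparison turns out null, its meaning depends on the power the study had, and the protocol does not let a reader work that out.

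**Working it through.** **Inputs, all from the protocol.** Two-sided alpha 0.05, power 80%, 1:1 allocation. Two-year risks p1 = 0.04 (usual care) and p2 = 0.8 × 0.04 = 0.032. Difference d = 0.008, mean risk 0.036. Attrition 20%. 600 patients per site.

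**1. Reproduce the table entry.** Two-proportion formula:

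n0 = [1.960 √(2 × 0.036 × 0.964) + 0.842 √(0.04 × 0.96 + 0.032 × 0.968)]² / 0.008² = (0.5164 + 0.2217)² / 0.000064 ≈ 8511 per group.

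With continuity correction:

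n = (n0/4) [1 + √(1 + 4/(n0 d))]² = (8511/4) (1 + √1.05875)² ≈ 8760 per group.

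This matches the table: 8760 per group, 17520 in total.

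**2. Attrition.** The table uses 17520 × 1.2 = 21024. To keep 17520 after losing 20%, the number randomised is 17520 / 0.8 = 21900, and 21900 / 600 = 36.5, so 37 sites. With 21024 randomised and 20% lost, power is about 78% (79.5% without continuity correction), a small shortfall.

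**3. Is it the most conservative scenario?** Harder cells in the same table, after the protocol's attrition factor:

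| Annual rate | Hazard ratio | Total |
|---|---|---|
| 0.02 | 0.80 (the scenario in the text) | 21024 |
| 0.02 | 0.85 | 38083 |
| 0.01 | 0.80 | 42811 |
| 0.01 | 0.85 | 77599 |

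**4. The range 6626-13762.** At 0.05 per year the table has 6626 before attrition and 7951 after. At 0.03 it has 11468 before and 13762 after. The quoted range takes its lower end before attrition and its upper end after. On the protocol's own inflated basis it is 7951-13762.

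**5. Power of that range in the 0.02 scenario.** With 20% loss, m = 0.4N patients per group remain, and

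power = Φ{[(d − 1/m) √m − 0.5164] / 0.2634}, where 0.2634 = √(0.04 × 0.96 + 0.032 × 0.968). The 1/m term is dropped for the uncorrected version.

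- N = 7951, m = 3180: 38% corrected, 40% uncorrected.
- N = 13762, m = 5505: 60% corrected, 62% uncorrected.

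**6. Power by number of sites.** Assumptions: 600 per site, 20% loss, two-year risks, hazard ratio 0.8, continuity-corrected. The numbers of sites are illustrations, because the visible text gives none.

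| Sites | Randomised | 0.02 per year | 0.03 per year | 0.05 per year |
|---|---|---|---|---|
| 10 | 6000 | 29% | 43% | 66% |
| 20 | 12000 | 54% | 72% | 92% |
| 30 | 18000 | 72% | 88% | 99% |
| 37 | 22200 | 81% | 94% | over 99% |

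**7. The hazard ratio column of the 13-year study (80 patients per arm).** All 14 entries equal usual-care events divided by 80, to rounding. Death: 40/80 = 0.50. Cardiovascular death: 18/80 = 0.225, printed 0.23. All cardiovascular events: 48/80 = 0.60. Blindness: 7/80 = 0.0875, printed 0.09. These are control-group event proportions. For comparison, the crude count ratio for all cardiovascular events is 25/48 = 0.52. The other two tables print no denominators. Their entries fit the same pattern (all six of the 2-year table with 114, both of the 7-year table with 80), but those denominators are inferred.

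**The case against.** **A reader might infer that the trial could not have detected the planned effect.** The documents do not show this. The number of sites is unknown, and 37 sites would give about 81% even at 0.02 per year. The true rate may also be higher: the protocol gives annual rates of 7%, 3%, 1.5% and 1% for its four risk groups and says that most patients enrolled earlier were at high or very high risk. The calculation above is somewhat cautious too. It counts exactly two years, while the protocol plans at least 24 months. If mean follow-up were 2.5 years (an assumption), 30 sites would give about 82% without continuity correction. All this stands. It makes the power undetermined. It does not supply the missing basis for a claim made at 0.02 per year.

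**A reader might take 6626-13762 as contradicting the 0.02 scenario.** It does not: the text assigns that range to 0.05 and 0.03 per year. The defects are its mixed attrition basis and the lack of any matching figure in the text for 0.02.

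**A reader might conclude from the mislabelled column that the 0.3 to 0.7 statement is false.** Crude count ratios for the composites fall inside it: 25/48 = 0.52, 14/34 = 0.41 and 20/30 = 0.67. The last two assume equal denominators, and the 2-year table compares patients by targets attained, not by randomised arm. The printed columns do not establish the statement, but nothing here refutes it. The sample size grid does not use those entries, so the labelling has no bearing on the power calculation.

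**Front pages and the study-flow figure are not in the text at hand.** A total may stand there. The point about the missing total is limited to the visible text, and the sentence claiming power would still need to cite that total.

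**Conclusion.** The point holds. At 0.02 per year and hazard ratio 0.8, the protocol's own table, reproduced exactly, requires 17520 evaluable patients: 21024 by its inflation, 21900 if 20% are lost. The visible text commits to no total, so the claim of sufficient power is unsupported. Calling the scenario the most conservative is wrong against the same table, where three harder cells need 38083 to 77599.

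The range in the next sentence, put on one attrition basis (7951-13762), would give about 38-62% power in the 0.02 scenario. That shows what happens if those totals are read across to the lower rate. It is not an estimate of this trial's power.

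The figures rest on two-year risks of 4% and 3.2%, 1:1 allocation, a two-sided 5% test and no information from patients who are lost. The mislabelled column is a secondary correction, certain for the 13-year table and probable for the other two.

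**What to change.** In the text of the sample size section:

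1. Delete the description of the scenario as most conservative and the unqualified claim of sufficient power.
2. State that 0.02 per year with hazard ratio 0.8 needs 17520 evaluable patients, or 21900 randomised with 20% loss.
3. Give the range for 0.05 to 0.03 per year on one attrition basis: 6626-11468 evaluable, which divided by 0.8 is 8283-14335 randomised (7951-13762 by the table's present factor of 1.2).
4. State the planned total or number of sites and the power it gives at 0.02, 0.03 and 0.05 per year, in the form of the table by sites above. If power at 0.02 is low, say that the event comparison at that rate will be reported mainly as an estimate with its confidence interval.

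As a secondary correction, relabel the hazard ratio column of the 13-year table as the usual-care event proportion, check the labels and denominators of the other two tables, and verify the 0.3 to 0.7 sentence against its sources before keeping or changing it.

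The cost is protocol wording and one short table. No procedure changes. The stated power may look less favourable than it does now.

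### The primary sample-size table takes twice the annual hazard as the 2-year risk and the hazard ratio as a risk ratio; at HR 0.8 and 2 years, the sizes labelled 80% power give about 76% at hazard 0.05 and 70% at 0.10 (minor)

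*Protocol*

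**What the plan says.** Protocol, Sample Size Calculation, Primary composite outcome. The aim is to "estimate the sample size needed to give a 2-year study 80% power with an alpha value of 0.05". The scenarios take an "annual hazard rate ranging from 0.01 to 0.10 in the usual care group and a HR ranging from 0.5 to 0.85".

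The conversion to two years is given in words: "Using the most conservative scenario where the annual hazard rate is 0.02, i.e. 0.04 in 2 years". The table applies it throughout. In the high and very high risk block the annual row reads "annaul hazard rate | 0.05 | 0.05 | 0.05 | 0.1 | 0.1 | 0.1" and the 2-year usual-care row reads "hazard rate (usual) | 0.1 | 0.1 | 0.1 | 0.2 | 0.2 | 0.2". The structured-care row is the usual-care row times the hazard ratio (0.08 and 0.16 at HR 0.8). The next row is the plain difference between the two.

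The text then concludes: "assuming a modest HR of 0.8 in the structured care group, a sample size of 6626-13762 patients will give the study 80% power". The 6626 is the table's total before attrition at hazard 0.05. The 13762 is the total after attrition at hazard 0.03.

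The Data Analysis section makes the test two-sided ("A p value of 0.05 or less (2-tailed) will be considered significant") and plans a Kaplan-Meier comparison for the primary endpoint.

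**The concern.** The inputs are called hazards and hazard ratios, and the primary comparison is time to event. Twice an annual hazard is a 2-year cumulative hazard, not a probability. The two are close when the hazard is small and separate as it grows. At hazard 0.10 the cumulative hazard is 0.20, but the risk is 0.181. A hazard ratio of 0.8 also gives a risk ratio somewhat nearer to 1.

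Both effects make the table's absolute differences, and so its numbers needed to treat, look better than the stated hazards imply. What is at stake is whether the 80% power claimed in the text and the table heading is right on the Protocol's own 2-year basis.

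**Working it through.** **Inputs (Protocol).** Two-sided alpha 0.05, power 80%, 1:1 allocation, HR 0.8, annual hazards h from the table, 2 years. Normal quantiles are 1.96 and 0.8416. Constant hazard is assumed, and loss is ignored because the sizes checked are those before attrition.

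**1. Reproduce the table.** Put p1 = 2h and p2 = 2h × 0.8 into the two-proportion formula with Fleiss continuity correction:

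- n0 = [1.96 √(2p̄(1 − p̄)) + 0.8416 √(p1(1 − p1) + p2(1 − p2))]² / (p1 − p2)², where p̄ is the mean of p1 and p2
- n = (n0/4) × [1 + √(1 + 4/(n0 × (p1 − p2)))]²

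At h = 0.05, p1 = 0.10 and p2 = 0.08 give n0 = 3212.9 and n = 3312.2, rounded up to 3313. At h = 0.10, 0.20 and 0.16 give n = 1496.5, rounded up to 1497. All five HR 0.8 cells match (17838, 8760, 5734, 3313, 1497), as do 13 of the 15 cells in the table. The two that do not are hazard 0.03 with HR 0.5 (stated 1067, computed 814) and with HR 0.85 (stated 13820, computed 10379). They are a separate matter.

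**2. Replace the proportions by 2-year risks.** q1 = 1 − exp(−2h) and q2 = 1 − exp(−1.6h).

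- h = 0.05: 0.0952 v 0.0769, difference 0.0183 (table 0.02), risk ratio 0.808
- h = 0.10: 0.1813 v 0.1479, difference 0.0334 (table 0.04), risk ratio 0.816

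**3. Size needed and power at the stated size.** The size uses the table's own formula. The power is the log-rank (Schoenfeld) value with d = n(q1 + q2) expected events: power = Φ(½ √d × |ln 0.8| − 1.96).

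Worked at h = 0.05: d = 3313 × 0.1720 = 570; ½ × √570 × 0.2231 − 1.96 = 0.704; power 75.9%. At h = 0.10: d = 493; the argument is 0.517; power 69.7%.

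| Annual hazard | Table n per group | n needed, same formula | Power at table n |
|---|---|---|---|
| 0.02 | 8760 | 9246 (+6%) | 79.3% |
| 0.03 | 5734 | 6221 (+8%) | 78.2% |
| 0.05 | 3313 | 3802 (+15%) | 75.9% |
| 0.10 | 1497 | 1992 (+33%) | 69.7% |

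An uncorrected two-proportion calculation agrees to within half a point (75.6% and 69.4% in the last two rows). At HR 0.5 the log-rank powers are 81.7% at 0.05 and 76.9% at 0.10 (79.0% and 74.4% on proportions), so less is lost there.

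**4. Events.** At HR 0.8, 4 × (1.96 + 0.8416)² / (ln 0.8)² = 630.5, so 631 events are needed. The table's sizes yield 570 at 0.05 and 493 at 0.10 within 2 years.

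**5. Longer follow-up.** If follow-up is spread uniformly from a to b years, the average risk at hazard h is 1 − [exp(−ha) − exp(−hb)] / [h(b − a)]. The structured-care arm uses 0.8h. Two windows are assumed, since the Protocol does not fix one:

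| Follow-up per patient | Power at 0.05 (n 3313) | Power at 0.10 (n 1497) |
|---|---|---|
| exactly 24 months | 76% | 70% |
| 24–31 months (7-month accrual, close-out at the last patient's month 24) | 81% | 75% |
| 28–36 months (8-month accrual, common close-out 3 years after first entry) | 86% | 80% |

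**The case against.** The strongest reply is that few patients stop at 24 months. The table's heading gives two years as a minimum. Study Design gives a total follow-up period of 2.5 to 3 years. Logistics and timeline has follow-up complete 3 years after the first patient enters. Outcomes are ascertained at close-out as well as at years 1 and 2. A Kaplan-Meier comparison can use later events. This stands: under the 28–36 month reading no shortfall remains at HR 0.8, and under 24–31 months only the 0.10 column falls short. But the table's doubling fixes the horizon at 2 years, and nothing in the section claims credit for more.

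Second, the rates. The same section estimates annual event rates of 7% for very high risk and 3% for high risk patients, below the 0.10 and 0.05 that the table uses under those labels. The text relies on 0.02, 0.03 and 0.05 and never on 0.10. This also stands. The Protocol says that most early enrolees were high or very high risk, but that does not put them in the 0.05 and 0.10 columns.

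Third, the word hazard may be loose: the section on validating the risk equations turns a 2% annual incidence into 4% over 2 years. If the rates are annual risks, compounding gives 1 − 0.95² = 0.0975 v 1 − 0.96² = 0.0784 in the 0.05 column, with power 78.4%. In the 0.10 column it gives 0.19 v 0.1536, with power 75.2%. The loss is smaller, but doubling is inexact on this reading too.

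A reader might infer that the trial is underpowered, or must recruit up to a third more patients. The documents do not support that. The sizes are scenarios, recruitment is set at 600 per site, that figure is justified on risk-factor outcomes, and no overall total is fixed from this table.

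**Conclusion.** The stated power is wrong on its own basis, by a modest amount. At HR 0.8, constant hazard and exactly 2 years, before attrition, the sizes labelled 80% give about 79%, 78%, 76% and 70% at hazards 0.02, 0.03, 0.05 and 0.10. The one or two points at 0.02 and 0.03 are immaterial beside the width of the assumed hazards and hazard ratios. The figure that matters is the 6626 at hazard 0.05, because the text itself attaches 80% power to it. The 70% concerns a table column that supports no statement in the text and lies above the Protocol's own highest estimated event rate, so it need not describe the expected case mix. Realistic follow-up may restore the power in full, depending on when the study closes. This is a minor correction to the sample-size justification, not evidence that the trial is too small.

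**What to change.** In the sample-size section for the primary outcome:

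- Declare the follow-up time t on which the table rests. If follow-up beyond 24 months is relied on, say so and state the close-out rule assumed.
- Recompute every column with risks 1 − exp(−ht) and 1 − exp(−ht × HR), including the absolute differences and numbers needed to treat. If the inputs are meant as annual risks, say so and compound them.
- State the required events, 631 at HR 0.8.
- Correct the sentence saying that "a sample size of 6626-13762 patients will give the study 80% power at an alpha value of 0.05", and the 0.05 and 0.10 columns, by restating either the sizes or the power at the stated sizes. On a strict 2-year basis with the table's formula, 3802 replaces 3313 and 1992 replaces 1497 per group. Give both ends of the range on the same footing, before or after attrition.

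The cost is a recalculation and restated figures. Recruitment, conduct and analysis do not change, and no extra patients are needed.
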